**Methods:**

This study is a community-academic partnership between University of California, San Diego and Haus of Volta, a nonprofit organization that promotes positive self-image in younger breast cancer survivors. This ongoing pilot study aims to recruit 30 younger breast cancer survivors across the United States (<55 years old, >6 months post primary cancer treatment, self-report <60 min of moderate-to-vigorous-intensity physical activity [MVPA]) into a 3-month peer-delivered, fully remote exercise program. Participants will complete 6 biweekly video chat sessions with a trained peer mentor, a fellow younger breast cancer survivor. Participants will receive a Fitbit Charge 3; weekly feedback on Fitbit data from their peer mentor; and access to a private, in-app Fitbit Community to provide and receive support from other participants and all peer mentors. At baseline, 3 months, and 6 months, participants will complete quality of life questionnaires, and MVPA will be measured using the ActiGraph accelerometer. Feasibility and acceptability will be explored through a mixed methods approach (ie, quantitative questionnaires and qualitative interviews). Intervention delivery and adaptations by peer mentors will be tracked through peer mentor self-evaluations and reflections, review of video-recorded mentoring sessions, and monthly templated reflections by the research team.

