### Study Objectives

This study will conduct a single-arm, pre-post pilot trial of Pink Body Spirit, a 3-month remotely delivered, peer-led physical activity intervention, in 30 younger breast cancer survivors. This community-academic partnership project has 3 aims: (1) explore the feasibility and acceptability of the pilot study methods using a parallel mixed methods approach (postintervention quantitative surveys and qualitative interviews), (2) assess the preliminary impact of the intervention on physical activity and quality of life, and (3) use a multimethod approach to explore the process of intervention delivery and adaptations by peer mentors. The overall goal is to develop an intervention that can be disseminated and used by Haus of Volta. This protocol paper reports on the rationale, methodology, and outcome measures of this ongoing community-academic partnership project.

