#### Preliminary Intervention Impacts on Physical Activity and Quality of Life

Descriptive statistics (mean [SD] and n [%] where applicable) will be calculated for each variable of interest at T0, T1, and T2. Separate paired *t* tests will assess changes in each variable of interest from T0 to T1 and T1 to T2. The level of significance will be set at α=.05. From the means and SDs, Cohen *d* will be calculated to determine the effect size. These data will allow us to estimate the sample size needed to detect clinically significant intervention effects at an α of .05 and power of 0.80, should the program be tested in a larger efficacy trial.

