### Future Directions

There are several potential future directions after the completion of this pilot trial. If the intervention shows preliminary benefit for physical activity and/or quality of life, the investigators may choose to test the program in an adequately powered efficacy trial based on effect sizes from this pilot study. Alternatively, the detailed process evaluation of program delivery and adaptations made by the peer mentors could inform a future hybrid-effectiveness implementation trial. A hybrid trial would facilitate a formal evaluation of the implementation process. Another possible outcome is that Haus of Volta will bring the Pink Body Spirit program directly into the community. Through this project, we aim to increase the skills of younger breast cancer survivors so that they can better support each other in making healthy lifestyle choices and improving well-being, in line with Haus of Volta’s mission to promote positive self-image and health in younger breast cancer survivors. We elected to use a publicly available web-based training program for the majority of the motivational interviewing skills training and recorded the in-person training to support fully remote training of 2 peer mentors. The length of the training was not a barrier to engaging peer mentors and supported the development of introductory-level skills. Furthermore, all study-specific web-based Zoom trainings (eg, research ethics, exercising safely after breast cancer, and supporting safe exercise goal setting) were recorded for future use. The extensive peer mentor trainings have provided leadership skills to the peer mentors not only to deliver the intervention as part of this research study but also to continue serving as advisers to younger breast cancer survivors in various capacities after the study ends. Engaging Haus of Volta in interpretation of the results will enhance self-efficacy for conducting research and understanding and disseminating results. Part of the goal of reviewing and interpreting the results as a community-research partnership is to develop ways to empower and support the younger breast cancer survivor community to continue the physical activity program and peer mentoring in an ongoing manner. Haus of Volta could use pilot findings to apply for more funding to sustain the program. Pilot study results will be summarized in lay language for use by Haus of Volta and partnering organizations and for dissemination in survivor-centered settings, further increasing the impact and outreach in the younger breast cancer survivor community.

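### The uncontrolled pre-post Cohen d from at most 30 women is put forward to size a later efficacy trial, which it is not fit to do

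*Protocol article*

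**What the plan says.** Study Objectives fixes the design: "This study will conduct a single-arm, pre-post pilot trial of Pink Body Spirit". The abstract gives the size: "This ongoing pilot study aims to recruit 30 younger breast cancer survivors". The inclusion criteria under Recruitment restrict entry to women who report under 60 minutes of MVPA a week.

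Under Preliminary Intervention Impacts on Physical Activity and Quality of Life, paired "tests will assess changes in each variable of interest from T0 to T1 and T1 to T2". Cohen d, from the means and SDs, "will be calculated to determine the effect size". The section then states the use: "These data will allow us to estimate the sample size needed to detect clinically significant intervention effects". The error rate and power for that calculation are given in the same sentence: "at an α of .05 and power of 0.80, should the program be tested in a larger efficacy trial".

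Future Directions makes the route explicit. If there is preliminary benefit, the investigators may choose to "test the program in an adequately powered efficacy trial based on effect sizes from this pilot study".

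The article names no important difference for MVPA, body image, sexual function or fatigue. Limitations links the small sample to generalizability and representativeness. It mentions neither the imprecision of d nor the lack of a control arm.

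**The concern.** Three separate problems stand between this d and a usable sample size.

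- **It targets the wrong quantity.** A controlled efficacy trial has to detect a difference between arms. The pilot d measures change within one arm and has nothing to subtract from it. Entry on low self-reported activity can produce regression to the mean. Recruitment began in September 2019 and final measures were expected in summer 2020, so season can move with follow-up. Time since treatment and reactivity to repeated measurement add to this. A control arm would share all of these.
- **It is imprecise.** With 30 women or fewer, the interval around d is wide. Required sample size varies with 1/d², which widens the range further.
- **An observed effect is not an important effect.** Sizing for a clinically significant effect needs a stated important difference. The d that a pilot happens to show does not supply one.

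At stake is the next trial. If it is planned on a favourable or uncontrolled d, it can be badly underpowered while appearing to have 80% power.

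**Working it through.** The article gives no expected d, SD, correlation, dropout rate or future sample size, so there is no figure of its own to reproduce. The check asks what the planned use would deliver under stated assumptions.

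**Inputs from the article:** single arm; 30 women; pilot tests at 5% ("The level of significance will be set at α=.05"); future trial at α .05 and power 0.80.

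**Assumptions:** two-sided α; later trial parallel, two-arm, 1:1; observed d = 0.5 standardised by the raw SD, with equal SDs at the two times; all 30 women complete; correlation r between baseline (T0) and 3 months (T1) of 0.5, 0.7 or 0.8.

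**Step 1. Sample size at the point estimate.** The normal approximation is n per arm = 2(1.960 + 0.842)²/d². At d = 0.5 this is 15.70/0.25 = 62.8. The exact two-sample t calculation gives **64 per arm**.

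**Step 2. Interval for d.** The exact (noncentral t) interval applies to dz, the mean change divided by the SD of change. The two scales are linked by d = dz × √(2(1 − r)). So I converted d = 0.5 to dz, took the 95% interval at n = 30, and scaled back. This is approximate for r other than 0.5, because it treats the SD ratio as fixed.

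| r | √(2(1−r)) | dz | 95% CI for dz | 95% CI for raw-SD d | n per arm at upper and lower limit |
|---|---|---|---|---|---|
| 0.5 | 1.000 | 0.50 | 0.12 to 0.88 | 0.12 to 0.88 | 22 to 1,166 |
| 0.7 | 0.775 | 0.65 | 0.25 to 1.04 | 0.19 to 0.80 | 26 to 431 |
| 0.8 | 0.632 | 0.79 | 0.37 to 1.20 | 0.24 to 0.76 | 29 to 282 |

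The ratio of the largest to the smallest sample size is about 53 at r = 0.5 (1,166/22), 17 at r = 0.7 (431/26) and 10 at r = 0.8 (282/29).

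**Step 3. Shared change.** Suppose controls would improve by 0.2 SD (assumed). The between-arm effect is then 0.5 − 0.2 = 0.3. The exact calculation gives **176 per arm** (normal approximation 15.70/0.09 = 174.4). A trial of 64 per arm would have **39% power** for an effect of 0.3.

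**Step 4. What the pilot can supply.** At n = 30 the 95% interval for an SD runs from √(29/χ²₀.₉₇₅) = 0.80 to √(29/χ²₀.₀₂₅) = 1.34 times the estimate. With the target difference fixed in advance, n scales with SD², so it varies from 0.63 to 1.81 times its point value. That is about threefold, against 10-fold to 53-fold when d itself is carried forward.

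**The case against.** The strongest reply is that little in this study turns on the sentence. The later trial is hypothetical, the investigators only may choose it, and Future Directions lists two alternatives: a hybrid implementation trial and direct community delivery. The feasibility, acceptability and process aims do not use d. A later trial would have its own protocol and sample size justification. All of this stands. A reader might infer that the flaw undermines the pilot or has to be fixed before it can proceed; the article does not support that.

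A second reply is that the data in question include the SDs, so sizing for an important difference with pilot SDs is compatible with the statistical section. Read alone, that section allows this. Future Directions does not, because it names effect sizes as the basis.

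Three other strong readings also fail:

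- **22 to 1,166 per arm as the range.** It holds only if r = 0.5. With a higher correlation and a raw-SD d the range is narrower, though still too wide to plan on.
- **The correlation is lost because d comes from means and SDs.** The paired t tests need the SD of change, and r follows from that and the two SDs. What gets tabulated is detail an article may leave to the full protocol or analysis plan.
- **The pilot cannot inform a sample size at all.** A number can be computed from d, and the SDs, correlation and retention are useful planning inputs. The objection is to using d as the target effect.

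**Conclusion.** The concern holds in this limited form and should be fixed. The article claims a property that the design lacks. A single-arm pre-post d from at most 30 women does not estimate the between-arm effect of a controlled trial, is too imprecise to fix its size, and does not define a clinically significant effect.

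The figures in the working are illustrations. The observed d, the correlation, full completion, the control-arm change and the two-arm design are assumptions, because the article gives none of them. The conclusion does not depend on one choice among these: at each correlation examined, the interval spans at least a tenfold or near-tenfold range of sample sizes, before any allowance for change in controls.

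**What to change.** In the section on preliminary intervention impacts, replace the last sentence with wording such as: *Cohen d will be reported descriptively, with its 95% confidence interval and the SD used to standardise it. For planning, the pilot will supply the SD of each outcome, the T0 to T1 correlation and retention, each with a 95% confidence interval. Any later efficacy trial will be sized on a prespecified clinically important between-group difference.*

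In Future Directions, replace the clause that bases the efficacy trial on pilot effect sizes with a matching statement: sized on a prespecified important between-group difference, with variability and retention informed by this pilot.

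The cost is two sentences and a few summary statistics from data already planned. The downside is that a later trial may come out larger than the pilot d would suggest.

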#### Multimethod Process Evaluation of Intervention Delivery and Peer Mentor Adaptations

All findings will be triangulated to deepen our exploration of the intervention delivery process and adaptations made by peer mentors throughout the study. Peer mentor field notes will be downloaded from REDCap and reviewed by [name]. She will record memos throughout her review and will prepare a separate summary of the field notes for each of the 5 peer mentors. At the end of the study, the 5 summaries will be synthesized in a single narrative summary. [name] will follow up with peer mentors directly if any of the field notes require further clarification. Video recordings of sessions will be reviewed using a template checklist of predetermined variables. Data from each category of the template (eg, adaptations, barriers to intervention delivery, and facilitators to intervention delivery) will be transferred to a matrix. At the end of the study, [name] will develop a narrative summary for each category. Templated reflections will also be synthesized in a narrative summary at the end of the project.

## Results

Recruitment began in September 2019. As of February 2020, the physical activity intervention is ongoing. Final measures are expected to occur in summer 2020, with mixed methods data analysis and results available in winter 2021.

### Future Directions

There are several potential future directions after the completion of this pilot trial. If the intervention shows preliminary benefit for physical activity and/or quality of life, the investigators may choose to test the program in an adequately powered efficacy trial based on effect sizes from this pilot study. Alternatively, the detailed process evaluation of program delivery and adaptations made by the peer mentors could inform a future hybrid-effectiveness implementation trial. A hybrid trial would facilitate a formal evaluation of the implementation process. Another possible outcome is that Haus of Volta will bring the Pink Body Spirit program directly into the community. Through this project, we aim to increase the skills of younger breast cancer survivors so that they can better support each other in making healthy lifestyle choices and improving well-being, in line with Haus of Volta’s mission to promote positive self-image and health in younger breast cancer survivors. We elected to use a publicly available web-based training program for the majority of the motivational interviewing skills training and recorded the in-person training to support fully remote training of 2 peer mentors. The length of the training was not a barrier to engaging peer mentors and supported the development of introductory-level skills. Furthermore, all study-specific web-based Zoom trainings (eg, research ethics, exercising safely after breast cancer, and supporting safe exercise goal setting) were recorded for future use. The extensive peer mentor trainings have provided leadership skills to the peer mentors not only to deliver the intervention as part of this research study but also to continue serving as advisers to younger breast cancer survivors in various capacities after the study ends. Engaging Haus of Volta in interpretation of the results will enhance self-efficacy for conducting research and understanding and disseminating results. Part of the goal of reviewing and interpreting the results as a community-research partnership is to develop ways to empower and support the younger breast cancer survivor community to continue the physical activity program and peer mentoring in an ongoing manner. Haus of Volta could use pilot findings to apply for more funding to sustain the program. Pilot study results will be summarized in lay language for use by Haus of Volta and partnering organizations and for dissemination in survivor-centered settings, further increasing the impact and outreach in the younger breast cancer survivor community.

### Conclusions

The proposed study represents a novel contribution to the literature by providing rich information on ways to promote increasing physical activity and potential benefits to quality of life for younger breast cancer survivors. This project benefits from the combined knowledge of the community regarding the challenges faced by young breast cancer survivors and the research team’s expertise in conducting physical activity interventions and mixed methods evaluations. As smartphone ownership is reported by the majority of Americans and is increasing across all race/ethnicity, income, and age groups [74], this technology-supported, peer-delivered intervention has the potential for broad reach in geographically diverse, younger breast cancer survivors.

## Appendix

Multimedia Appendix 1 California Breast Cancer Research Program grant review.

## Abbreviations

BIS: Body Image Scale
CITI: Collaborative Institutional Training Initiative
FSFI: Female Sexual Function Index
HIPAA: Health Insurance Portability And Accountability
MVPA: moderate-to-vigorous-intensity physical activity
PAR-Q: Physical Activity Readiness Questionnaire
PI: principal investigator
T0: baseline
T1: postintervention
T2: follow-up
UC San Diego: University of California, San Diego
